### Outcomes

3.3

The primary outcome of the study is adherence to neurology clinic appointments. This is defined as the number of appointments attended as scheduled and on time by the participant, as reported by the investigator.

Secondary outcomes are as follows:
Percent of PWE who achieve seizure freedom.Seizure frequency reduction: The percentage decrease in number of monthly seizures from baseline to the study endpoint of 360 days.

A complete list of outcomes can be found in Table 2.

**TABLE 2 epi412889-tbl-0002:** Primary, secondary, and exploratory outcomes of interest.

Outcome category	Outcome	Definition	Method of measuring
Primary	Adherence to Neurology Clinic Appointments	The number of appointments attended as scheduled and on time by the participant	Investigator reported
Secondary	Seizure freedom	% of PWE who achieve seizure freedom, or the ability to live without seizures of any type	Seizure diary counts
Secondary	Seizure frequency reduction	The percentage decrease in the number of monthly seizures from baseline to the study endpoint of 360 days	Seizure diary counts
Exploratory	Quality of life in epilepsy	A standardized scale and subjective report of physical, social, and psychological well‐being by a person with epilepsy	Patient/parent reported
Exploratory	Number of visits to traditional healers	Self‐reported number of visits to non‐allopathic providers for epilepsy management	Patient reported
Exploratory	Self‐reported adherence to ASMs	The number of pills left in the medication bottle, determined as a medication possession ratio	Investigator Counted
Exploratory	Stigma scale in epilepsy	A standardized scale and subjective report of stigma perceived by a person with epilepsy	Patient reported
Exploratory	Days attended at work or school	Self‐reported days attending school or work by a person with epilepsy of the past 90 days	Patient reported
Exploratory	Number of unintentional injuries due to seizures	Including burns, fractures, head injury, and related injuries in the past 90 days	Patient reported
Exploratory	Number of status epilepticus events	Reported by participant and family member in a log, articulating a seizure episode lasting >5 min	Patient reported

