### Participant timeline

3.4

The timeline of screening, enrolment, and interventions is provided in Table 3. The interventions will be provided at follow‐up visits taking place every 90 days. The baseline visit will include a neurologist's description of seizure history, including seizure semiology, epilepsy diagnosis, and etiology of epilepsy to the degree possible given resource limitations. Structured forms will be used. Several measures will be collected during follow‐up visits, including detailed seizure information, quality of life surveying, medication possession, stigma scale surveying using the Stigma Scale of Epilepsy (SSE),^26^ health visit history, school/work attendance, and injury surveying.

**TABLE 3 epi412889-tbl-0003:** Schedule of tests and events at each study visit.

	Screening	Baseline	90	180	270	360
Study visit		1	2	3	4	5
Informed consent	×					
Assess inclusion and exclusion criteria	×	×				
Medical history	×	×				×
Seizure diary		×	×	×	×	×
Concomitant medication history		×		×		×
Quality of Life in Epilepsy‐31 scale		×	×	×	×	×
Consumption and household assets module		×				×
Stigma Scale of Epilepsy		×	×	×	×	×
Medication possession ratio, as appropriate based on assigned arm			×	×	×	×
Health visit history (allopathic and traditional)		×	×	×	×	×
School/work attendance log		×	×	×	×	×
Injury survey		×	×	×	×	×
Status epilepticus query		×	×	×	×	×
Body weight, height, heart rate		×				×
Urine pregnancy test (for people of childbearing potential), *as needed	×	*	*	*	*	*
Clinical labs (including serum Na+, glucose), *as needed	*	×	*	*	*	*
Brain MRI	×					×
Conditional cash allocation, as appropriate based on assigned arm		×	×	×	×	×
Vitality status assessment			×	×	×	×

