### Plans for assessment, collection of outcomes, and data management

5.1

Data will be collected from the baseline visit and follow‐up visits (Table 3). An enrollment survey is provided in Appendix S2. All investigators will receive research ethics and data quality control training to ensure adherence to proper documentation and data collection. Data quality control measures will be implemented by the U.S. and Guinean staff on a weekly basis to ensure accuracy. Missing data will be addressed throughout the study. Use of REDCap™ with forced responses to progress to the next page will be used for surveys to avoid missingness. Other data points that are missing in a systematic way will be re‐evaluated for any clinical or cultural reasons. No data imputation will occur.

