### Plans to promote participant retention and complete follow‐up

5.2

The study investigators will provide a careful explanation of the importance of follow‐up visits before a prospective participant gives informed consent. Participants will be asked to follow up in person and reminded of upcoming visits approximately a week in advance. Participants will also be given access to a study phone number and allowed to attend their visit ±7 days of the scheduled date to accommodate personal, work, and/or public transit schedules and further promote retention.

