## DISCUSSION

8

Our study provides a concrete plan to disaggregate issues contributing to the epilepsy treatment gap and target simple interventions addressing three major presumed reasons for the treatment gap: low epilepsy awareness, limited access to ASMs, and absolute poverty. Our approach provides a new pathway and model for clinicians and researchers to consider this problem. This study comes at a time when the international community is searching for effective mechanisms of alleviating the burden of epilepsy globally. The *Intersectoral Global Action Plan on Epilepsy and Other Neurological Disorders 2022–2031* emphasizes the need for concerted, interdisciplinary action to enhance epilepsy care and treatment in the near term (“Draft Intersectoral global action plan on epilepsy and other neurological disorders 2022–2031,”^7^). CCT interventions, if proven to be effective for epilepsy care, could serve as a powerful tool for these global efforts.

There are several strengths to this proposed study. The study design is both ethical and appropriate for low‐resource populations and, if successful, could be programmatically scaled to other locations. We also propose the first test of CCT, a method that has been used in other conditions, such as HIV/AIDS^31^ and TB,^32^ and in vaccination campaigns, to address low uptake. The use of CCT is controversial and untested in PWE but could serve as a poverty‐reduction intervention in addition to improving health outcomes among PWE. Though commonly tested for other health‐focused outcomes and in other regions, there is no published research on CCT programs in neurological disorders to our knowledge and only a limited sample of tested CCT interventions in West Africa.^33^, ^34^

There are also several limiting factors to the study design. Though participants are blinded to the hypothesis of the study, there is a possibility of participants disclosing information on their allocation to other participants, which would reduce allocation blindness. There is also a risk of differential attrition between the study arms. Several study outcomes are participant‐reported, which require clear and proactive communication with participants.

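### The fixed 90-day look-back drops seizure injuries from the roughly 90 days before a missed visit when a later visit is attended (exploratory outcome; minor)

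*Protocol article*

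**What the plan says.** Table 2 in Section 3.3 lists the number of unintentional injuries due to seizures as one of seven exploratory outcomes. It is patient reported and defined as "Including burns, fractures, head injury, and related injuries in the past 90 days". The work or school outcome in the same table uses the same span: "days attending school or work by a person with epilepsy of the past 90 days".

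Table 3 in Section 3.4 places the injury survey at baseline and at days 90, 180, 270 and 360, and nowhere else. Section 5.2 lets participants vary the date; they are "allowed to attend their visit ±7 days of the scheduled date".

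Missed visits are expected. The primary outcome is "the number of appointments attended as scheduled and on time by the participant", and Section 3.2 makes the cash payment conditional on attending. Section 5.1 adds: "No data imputation will occur". Nothing in the article extends the look-back to the last attended visit or sets a catch-up question after a missed one. By contrast, Table 2 has status epilepticus events kept in a log, without a 90-day limit.

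**The concern.** A 90-day recall covers follow-up fully only if every visit takes place, and takes place 90 days after the one before. When a visit is missed, the next survey does not reach back to the last attended visit, so part of follow-up is never asked about.

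Two features make this worth raising here. First, an injury may itself be the reason for the missed visit, and that injury is the one left out. Second, attendance is what the cash intervention targets, so how completely injuries are captured could depend on the arm.

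The Introduction names frequent injuries, and deaths from injury, among the consequences of untreated epilepsy, and Table 1 shows that 74% of adults in the earlier cohort had been injured in a seizure. The stake is an exploratory harm measure; no primary or secondary conclusion depends on it.

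**Working it through.** **Inputs.** Look-back of 90 days (Table 2); visits at days 90, 180, 270 and 360 (Table 3); window of ±7 days (Sections 3.2 and 5.2). The plan states no figure for injury ascertainment, so there is none to reproduce on this point.

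**1. All visits attended.** The day-90 window is 83 to 97 and the day-180 window 173 to 187.
- Longest interval: 187 − 83 = 104 days, so 104 − 90 = 14 days are uncovered.
- Shortest interval: 173 − 97 = 76 days, so 90 − 76 = 14 days are counted twice.
- Worst case over the year (visits on days 83, 187, 263 and 367): 14 + 14 = 28 uncovered days of 367, with 14 counted twice.
- If visit days are assumed uniform within the window, simulation gives on average 9.3 days uncovered and 7.4 counted twice. The two largely cancel.

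**2. One visit missed, the next attended.** With visits otherwise on schedule, the interval is 180 days and 180 − 90 = 90 days are uncovered, which is 90/360 = 25% of follow-up. At the window limits the interval is 277 − 83 = 194 days, with 194 − 90 = 104 uncovered. Two consecutive misses followed by an attended visit leave 180 days uncovered. The lost period is the one before the missed visit; what follows it lies within the next look-back.

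**3. Example.** A participant is burned on day 175, misses the day-180 visit and next attends on day 277. The look-back starts on day 277 − 90 = 187, so the burn is outside the outcome.

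**4. Last visit missed.** If day 360 is missed and nothing follows, the last 90 days are lost under any look-back. That loss is not caused by the 90-day rule.

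**5. What a longer look-back would recover.** The article gives no per-visit attendance, so assume independent attendance with probability p at each of four visits. The uncovered share is 1 − p with a fixed 90 days. Asking since the last completed visit, it is [(1−p) + (1−p)² + (1−p)³ + (1−p)⁴]/4.

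| Assumed p | Fixed 90 days | Since last visit |
|---|---|---|
| 95% | 5.0% | 1.3% |
| 90% | 10% | 2.8% |
| 78% | 22% | 7.0% |
| 70% | 30% | 10.6% |

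The remainder follows the last attended visit. If all missingness were permanent dropout, the longer look-back would recover nothing.

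**6. Illustration of distorted totals.** Assume equal true injury rates, attendance of 90% in one arm and 78% in the other, and raw totals with missed visits contributing zero. The ratio of recorded totals is 0.78/0.90 = 0.87 with the fixed look-back, and (1 − 0.0703)/(1 − 0.0278) = 0.96 with the longer one. The 90% is the 12-month retention assumed in Section 6, and 78% is that figure less the 12-point non-inferiority margin. Neither is a forecast of per-visit attendance.

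**The case against.** A reader might infer that the between-arm injury comparison is biased by a ratio of 0.87 (or 1.15 the other way up). The article does not support that. Section 6 names no injury test. Its only longitudinal method is a mixed model of the visit observations, and nothing is imputed. In such a model a missed visit is missing, not zero, and each attended visit supplies a count over the same 90 days. With equal rates and attendance unrelated to injury, the expected ratio is then 1.00. The 0.87 also includes loss at the end of follow-up that no look-back recovers, and 78% is a margin that the trial is meant to rule out. This objection stands, except that a per-visit model does not cure the case where the injury causes the missed visit.

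Nor does the article say that one arm will miss more intermediate visits. The Discussion says "There is also a risk of differential attrition between the study arms", but attrition ordinarily means dropout, and Section 1.2 hypothesises similar retention.

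It would also go too far to say that these injuries are never recorded anywhere. Changes in health status are recorded (Section 2.2), the monitoring board reviews adverse events (Section 7.1), and Table 3 has a health visit history at each visit and a medical history at day 360. Some injuries may surface there, but none of these sources is tied to the injury outcome.

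Finally, a fixed recall has merits: it matches baseline and keeps exposure constant. A variable recall could add under-reporting that differs by arm if attendance differs. That is a real cost, and it is why the longer recall suits memorable events and not day counts. For work or school days the gap is also less certain, because Table 3 lists an attendance log.

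**Conclusion.** The concern holds as a minor design point. Applied as written, Table 2 excludes about 90 days (25% of 360) of injury history whenever one of the first three follow-up visits is missed and the next is attended, and up to 104 days at the window limits. The arithmetic needs only the stated look-back, schedule and window.

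That the loss is informative rests on the plausible assumption that some injuries cause missed visits. Distortion between arms needs intermittent attendance to differ by arm and injury totals to be compared. The article settles neither, so direction and size are unknown. The visit window alone is not a material problem, and dropout loss is a separate matter. The outcome is exploratory, which limits the weight of the point.

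**What to change.** On the follow-up injury form and in Table 2, ask for injuries, with approximate dates, *since the last completed study visit*, and show that visit's date on the form. Keep 90 days at baseline, where there is no earlier visit. Because dates are collected, the present 90-day count can still be derived.

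Compare arms as injuries per person-day covered, for example with log days since the last completed visit as an offset. After permanent dropout, exposure ends at the last attended visit.

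Leave work or school days at the fixed 90-day recall, because days attended cannot be recalled reliably over half a year, and analyse them per day covered.

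The cost is a change of wording and a date field on one form, plus an exposure term in the analysis. The downside is recall of about 180 days after one missed visit (up to 194 at the window limits). That is acceptable for burns, fractures and head injuries, and the derived 90-day count allows a check on whether longer recall changes the picture. The change belongs before or early in follow-up, because what was not asked cannot be restored in the analysis.

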### Participant timeline

3.4

The timeline of screening, enrolment, and interventions is provided in Table 3. The interventions will be provided at follow‐up visits taking place every 90 days. The baseline visit will include a neurologist's description of seizure history, including seizure semiology, epilepsy diagnosis, and etiology of epilepsy to the degree possible given resource limitations. Structured forms will be used. Several measures will be collected during follow‐up visits, including detailed seizure information, quality of life surveying, medication possession, stigma scale surveying using the Stigma Scale of Epilepsy (SSE),^26^ health visit history, school/work attendance, and injury surveying.

**TABLE 3 epi412889-tbl-0003:** Schedule of tests and events at each study visit.

	Screening	Baseline	90	180	270	360
Study visit		1	2	3	4	5
Informed consent	×					
Assess inclusion and exclusion criteria	×	×				
Medical history	×	×				×
Seizure diary		×	×	×	×	×
Concomitant medication history		×		×		×
Quality of Life in Epilepsy‐31 scale		×	×	×	×	×
Consumption and household assets module		×				×
Stigma Scale of Epilepsy		×	×	×	×	×
Medication possession ratio, as appropriate based on assigned arm			×	×	×	×
Health visit history (allopathic and traditional)		×	×	×	×	×
School/work attendance log		×	×	×	×	×
Injury survey		×	×	×	×	×
Status epilepticus query		×	×	×	×	×
Body weight, height, heart rate		×				×
Urine pregnancy test (for people of childbearing potential), *as needed	×	*	*	*	*	*
Clinical labs (including serum Na+, glucose), *as needed	*	×	*	*	*	*
Brain MRI	×					×
Conditional cash allocation, as appropriate based on assigned arm		×	×	×	×	×
Vitality status assessment			×	×	×	×

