### Objectives

1.2

The primary objective is to implement and test a novel strategy to improve outcomes across the epilepsy care cascade marked by (1) retention in epilepsy care, (2) adherence to ASMs, and (3) seizure reduction with the measured goal of seizure freedom.

The first aim is to compare free ASMs vs. conditional cash using the epilepsy cascade of care. We hypothesize that the provision of free medication versus conditional cash will lead to (1) similar retention in epilepsy care—90% of PWE—at 360 days (Hypothesis 1a), (2) 80% of PWE regularly taking ASMs at 360 days (Hypothesis 1b), and (3) 65% of PWE achieving seizure freedom 360 days postenrollment (Hypothesis 1c).

The secondary aim is to detail facilitators and barriers to free medication versus conditional cash to improve seizure freedom among PWE. We hypothesize that barriers and facilitators to the uptake of each intervention strategy can be learned through careful, structured documentation by healthcare workers during study visits using an investigator‐designed written intake form as well as free‐text responses, serving as foundational information for a future larger‐scale implementation study in low‐resource populations.

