For Hypothesis 1b, we will use a one‐sample proportion test to test the null hypothesis that the percentage of PWE regularly taking ASMs at 12 months in the conditional cash arm is less than or equal to 85%, and we will use a two‐sample proportion test for the null hypothesis that the percentage of PWE regularly taking ASMs in the conditional cash arm is less than or equal to the percentage of PWE regularly taking ASMs in the free medication arm. For Hypothesis 1c, we will use a one‐sample proportion test to test the null hypothesis that the percentage of PWE with seizure freedom at 12 months in the conditional cash arm is less than or equal to 65%, and we will use a two‐sample proportion test for the null hypothesis that the percentage of seizure freedom in the conditional cash arm is less than or equal to the percentage of seizure freedom in the free medication arm.

To leverage the longitudinal observations collected during follow‐up visits at 90, 180, 270, and 360 days, we will use a generalized linear mixed effects model which allows us to study the association between multiple baseline variables (e.g., including the intervention options, education level, medication status, ASM type, distance to the study clinics) while accounting for the correlation between longitudinal observations.

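### Table 3 makes the only defined ASM adherence measure depend on the assigned arm, although both Hypothesis 1b tests need it in the cash arm and one needs it on the same scale in both arms

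*Protocol article*

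**What the plan says.** Adherence to ASMs is the second element of the primary objective (Section 1.2) and the subject of Hypothesis 1b. Section 6 sets two tests:

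- a one-sample test in the cash arm, with the null that "the percentage of PWE regularly taking ASMs at 12 months in the conditional cash arm is less than or equal to 85" per cent;
- a two-sample test, with the null that the cash-arm percentage is "less than or equal to the percentage of PWE regularly taking ASMs in the free medication arm".

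Table 2 (Section 3.3) defines one adherence measure: "The number of pills left in the medication bottle, determined as a medication possession ratio". It states no arm restriction. The outcome's name calls it self-reported, while the measurement column says the investigator counts it.

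The text of Section 3.4 also has no arm restriction: "Several measures will be collected during follow‐up visits, including detailed seizure information, quality of life surveying, medication possession" and other items. Table 3, in the same section, schedules the measure at days 90, 180, 270 and 360 as "Medication possession ratio, as appropriate based on assigned arm". The only other row with that qualifier is "Conditional cash allocation, as appropriate based on assigned arm".

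On supply, Section 3.2 provides ASMs free in the medication arm. Section 3.1 gives cash-arm participants an ASM recommendation and advice on buying.

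**The concern.** Both 1b tests need the percentage regularly taking ASMs in the cash arm, and the two-sample test needs it built the same way in each arm. Table 3 is what sites work from at a visit. On the cash row its qualifier plainly means one arm only. A site that reads the adherence row the same way would not count pills in the cash arm, and neither 1b test could then be computed.

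A site that does count in both arms still meets a difference in supply. Pills left in a bottle give pills taken only when the starting quantity is known. The study knows it for drug it dispensed. For drug bought outside, the document describes no record of the amount. Each arm's figure could then rest on a different construction, and the between-arm test would mix that difference with a difference in behaviour. A later analysis plan cannot recover data that the visits did not collect.

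**Working it through.** **1. The plan's own figures.** No sample size or power is stated for 1b; Section 6 sizes the trial on Hypothesis 1a. Those figures reproduce at one-sided 0.025 (0.05 split over two tests), 80% power and a 90% rate:

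- One-sample, margin 8.5%: 0.9 × 0.1 × (1.960 + 0.842)² / 0.085² = 97.8, so 98 (stated 98).
- Two-sample, margin 12%: (0.09 + 0.09) × (1.960 + 0.842)² / 0.12² = 98.1, so 99 (stated 99).

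Nothing in this point changes them.

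**2. The passages side by side.**

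| Place | Adherence measured in which arm? |
|---|---|
| Section 6, one-sample 1b test | Cash arm required |
| Section 6, two-sample 1b test | Both arms, same scale required |
| Table 2 definition | No restriction stated |
| Section 3.4 text | No restriction stated |
| Table 3 row | Depends on assigned arm |

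The seizure diary, quality of life, stigma, injury and attendance rows of Table 3 carry no arm qualifier. The adherence row was therefore marked as different, and no passage says how.

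**3. How much a recording difference matters.** Inputs: 100 per arm (200 randomized 1:1). Assumptions: a pooled z-test at one-sided 0.05, since Section 6 gives no level for 1b; true rates of 80% in both arms, or 92% cash versus 80% free; and recording differences of 5 and 10 points. With recorded rates pc (cash) and pf (free), and m their mean:

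- SE0 = √(2m(1 − m)/100)
- SE1 = √((pc(1 − pc) + pf(1 − pf))/100)
- P(reject) = 1 − Φ((1.645 × SE0 − (pc − pf)) / SE1)

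Worked cases:

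- True 92% vs 80%, recorded correctly: SE0 = 0.0491, SE1 = 0.0483, z = −0.81, power 79% (80% by exact enumeration).
- Free arm over-recorded by 5 points (92% vs 85%): SE0 = 0.0451, SE1 = 0.0448, z = 0.09, power 46% (47% by enumeration).
- True 80% vs 80%, cash arm over-recorded by 5 points (85% vs 80%): SE0 = 0.0537, SE1 = 0.0536, z = 0.72, false-positive rate 23.7%.

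| Truth (cash vs free) | Recording difference | P(declare cash better) |
|---|---|---|
| 92% vs 80% | none | 80% |
| 92% vs 80% | free arm +5 points | 47% |
| 92% vs 80% | free arm +10 points | 13% |
| 80% vs 80% | none | 5.0% |
| 80% vs 80% | cash arm +5 points | 23.7% |
| 80% vs 80% | cash arm +10 points | 63.3% |
| 80% vs 80% | free arm +5 points | 0.5% |

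The 92% rows are by enumeration and the others by the formula. At one-sided 0.025, over-recording the cash arm by 5 or 10 points gives 15.1% or 50.8%.

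**4. Direction.** The two-sample null is that cash is no better than free medication. Over-recording the free arm therefore makes a false claim for cash rarer and costs power. Over-recording the cash arm inflates false claims. The document does not show which would occur.

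**The case against.** The best defence is that the qualifier may only mean adapting the count to how each arm obtains its drug. No passage says the cash arm is left out. Table 2 and the Section 3.4 text are unrestricted, and because Section 6 tests 1b in the cash arm, the adaptive reading fits the rest of the document better. Table 3 also takes a concomitant medication history at baseline, day 180 and day 360 without an arm qualifier. This stands as far as it goes: a reader might infer that the cash arm will have no adherence data, and the documents do not establish that. But the adaptive reading still leaves the method in the cash arm undescribed. The medication history is not named as an adherence measure and is not taken at days 90 or 270.

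Two further inferences are tempting and unsupported:

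- That possession is nearly complete in anyone given a free supply. Table 2 counts pills left, so a participant who skips doses has pills left over.
- That, if 75% of pills were taken, the artefact would be 25 percentage points. Share of pills is an average per person, whereas 1b concerns the percentage of people regularly taking ASMs. Converting one to the other needs a cut-off and a distribution, and neither is given.

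It is also fair that a condensed article may leave the cut-off for regular use to the full protocol or analysis plan, and that ranking adherence as exploratory is a separate choice. Neither carries this point.

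**Conclusion.** The point holds as a conflict between current passages: Table 3 makes the only defined adherence measure arm-dependent, while Table 2 and both 1b tests presuppose one measure available in both arms. Because supply differs by arm, comparability is not secured even if both arms are counted, unless purchases are recorded. The documents do not show that the cash arm goes unmeasured, nor which arm's adherence would be overstated.

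The size is an illustration, not an estimate of actual bias. It rests on the assumed true rates, test level and recording differences given above. Under those, a 5-point difference in how the arms are recorded is enough to cut power from 80% to 47%, or to raise a 5% error rate to about 24%. The fix should be made before follow-up data are collected. The retention hypothesis and the sample size are unaffected.

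**What to change.** - In Table 3, strike the arm qualifier from the medication possession row.
- At days 90, 180, 270 and 360, record three quantities identically in both arms: pills obtained since the last visit (dispensed or bought), pills remaining and pills prescribed.
- Compute pills taken over pills prescribed, apply one common definition of regularly taking ASMs, and use the result for both 1b tests.
- In Table 2, correct the self-reported label so that it agrees with the investigator count.

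The cost is a few extra minutes at visits already scheduled. Cash-arm participants must bring their packs and recall what they bought, so some recall error will remain in that arm. The change concerns data collection only and does not alter treatment or the sample size.
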